Empirical research suggests that elite athletes involved in lean-sensitive or weight-sensitive sports are at elevated risk of developing an ED.^1 28^ In 2020, one of the first papers on EDs and climbing ability was published, which assessed 604 rock climbers (ages 32±9 years). It presented demographic data according to the International Rock-Climbing Research Association’s (IRCRA) directives.^29^ The results showed that higher level rock climbers had significantly lower BMI among both genders, and that 8.6% of the rock climbers reported DE behaviours. Additionally, 4.2% reported having been treated for an ED and there was an increased risk for EDs among female elite rock climbers compared with males.^30^ Strand^31^ states in a study of conversations in climbing communities that conversations related to achieving or maintaining low weight and lean body shape for performance enhancement purposes are common. Furthermore, Strand advises clinicians to be attentive to ‘weight talk’ in the climbing community.

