### Instruments

The first portion of the questionnaire aims to confirm that participants are eligible for inclusion, with a climbing level of advanced or above as classified by IRCRA. Demographic data will be gathered and reported including factors such as age, time practising the sport, amount of weekly training hours, climbing level and gender. Symptoms related to eating disturbances, RED-S, body image, compulsive training, perfectionism, mental health problems, sleep quality, overuse injuries and menstrual dysfunction will thereafter be measured (see table 1).

**Table 1 T1:** Measurements in the CLIMB-study.

Variable	Instrument	Baseline	Follow-up (6 months, 1, 2, 3 and 5 years postbaseline)
Eating disorder symptoms	The Eating Disorders Questionnaire (Fairburn and Beglin, 1994)^33^	X	X
Overuse injuries	The Oslo Sports Trauma Research Centre Overuse Injury Questionnaire (Clarsen *et al*, 2013)^35^	X	X
Perfectionism	The Frost Multidimensional Perfectionism Scale (Frost *et al)*^36^	X	X
Compulsive training	The Compulsive Exercise Test (Taranis *et al*)^39^	X	X
Body dissatisfaction	Body Shape Questionnaire, brief version (Welch *et al*)^41^	X	X
Mental health	Depression Anxiety Stress Scale-21 (Lovibond and Lovibond)^44^	X	X
Sleep quality	The Pittsburg Sleep Quality Index (Carpenter and Andrykowski)^46^	X	X
Symptoms of relative energy deficiency	Relative Energy Deficiency in Sports: RED-S (Edlund Health Q, Edlund, 2020)^50^	X	X
Physical activity and sedentary behaviour	Indicator Questions from the Swedish National Board of Health and Welfare	X*	
Bone density	DEXA	X†	

*Physical activity and sedentary behaviour will only be performed on the control group.

†DEXA will only be performed on a proportion of rock climbers.

DEXA, dual-energy X-ray absorptiometry.

In addition to the web-based questionnaire, bone health using dual-energy X-ray absorptiometry (DEXA) will be measured for climbing participants at baseline.

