### Statistical methods

#### Sample size

No previous data on injury incidence based on overuse injuries exist for rock climbers. Based on previous retrospective data from rock climbers,^49^ using a power of 80%, a significance level of 5% and an expected relative risk of 1.5 for the primary outcome, we calculated that approximately 55 participants were needed in each group (rock climbers and control group).

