### Outcome

The outcome ED will be measured with the EDE-Q. The EDE-Q consist of four subscales, restrained eating, eating concern, shape concern and weight concern addressing core dimensions of EDs. A score of >4 is indicative of an ED, and for the present study a score of >2.5 will be used as an indication of subclinical eating disturbances. Thus, higher scores are indicative of more severe symptoms of ED pathology.

Our primary outcomes are EDs symptoms measured with EDE-Q and overuse injuries measures with OSTRC-O. Our secondary outcomes are bone density (DEXA), symptoms of RED-S (Edlund Health Q), mental health problems (Depression, Anxiety and Stress Scale), sleep quality (PSQI), perfectionism (FMPS), CET and body dissatisfaction (BSQ-8).

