### Data analysis plan

Multinominal logistic regression analyses will be used to determine the associations between each of the exposures and trajectories of outcomes. The associations as ORs and 95% CIs will be reported. Bivariate models to measure the crude associations between the exposures and trajectories will be built.

The differences between the rock climbers and controls regarding the above-mentioned outcome measure ED will be analysed using multivariate analysis of variance (MANOVA). Both within-group and between-group analysis will be conducted. Further analyses among rock climbers with high ED versus low ED will be compared in relation to bone density, injuries, mental health and symptoms of RED-S. The MANOVA will be used for that purpose. A one-way repeated measures ANOVA will be used to identify changes over the 2-year span in the two groups of rock climbers with high ED versus low ED. In cases where overall significant changes are detected, post hoc analysis will be applied to specify where the between-group differences exist.

Structural equation modelling will be used at a later stage to investigate if the variables body image, injuries, mental illness, sports environment, bone density (from baseline) and EDs can predict injuries.

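### The comparison of high-ED with low-ED climbers splits a graded EDE-Q score and lists partly measured bone density with questionnaire outcomes under MANOVA; a continuous EDE-Q predictor with a separate bone model would lose less information

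*Protocol article*

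**What the plan says.** The secondary hypothesis (Introduction) is that climbers with more eating disturbance have worse health: lower bone density, more overuse injuries, more depression and so on. In the Data analysis plan the corresponding analysis is that "rock climbers with high ED versus low ED will be compared in relation to bone density, injuries, mental health and symptoms of RED-S", followed by "The MANOVA will be used for that purpose". The same two groups are then carried into a repeated-measures ANOVA over two years.

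On the score being split, the Outcome section says that "higher scores are indicative of more severe symptoms of ED pathology", and that "for the present study a score of >2.5 will be used as an indication of subclinical eating disturbances", with a score above 4 for an eating disorder. Neither cut-off is tied to the high/low comparison.

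On bone density, a footnote to Table 1 (Instruments) says that "DEXA will only be performed on a proportion of rock climbers". The text under the table says that bone health "will be measured for climbing participants at baseline" and states no such limit. The questionnaire outcomes are collected from all climbers.

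**The concern.** There are two separate problems in one planned analysis.

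First, the hypothesis is about a gradient and EDE-Q measures a gradient, but the analysis replaces the score with a two-level factor. Climbers just above and just below the cut are treated as different, and all climbers on one side as alike. If the cut is far out in the distribution, one group is also small.

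Second, standard MANOVA uses only people with every outcome present. Grouping bone density with injuries, mental health and RED-S symptoms would restrict all four comparisons to climbers who had a scan, although the other three outcomes exist for everyone. The result would then describe whoever was scanned.

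At stake is whether the secondary hypothesis is tested with the information the study collects, or with an avoidably smaller part of it.

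**Working it through.** **Inputs from the article.** Needed number: "approximately 55 participants were needed in each group" (Sample size). Prevalence of disordered eating: "8.6% of the rock climbers reported DE behaviours" (Introduction); 6.3% of men and 16.5% of women (Discussion). Candidate cut-offs: above 2.5 and above 4. DEXA share: not given.

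**The plan's own figure.** The 55 per group is for climbers against controls at a relative risk of 1.5, not for this comparison. It cannot be reproduced because no baseline risk is stated; a two-sided calculation without continuity correction gives 55 only if the control risk is about 0.505 to 0.515. It is used below only as a plausible number of climbers, beside an assumed 200.

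**1. Information kept by the split.** For a normally distributed score with a linear relation to the outcome, a cut leaving a share p in the high group keeps E = φ(z)² / [p(1 − p)], where z is the upper-p normal quantile.

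| p | z | φ(z) | p(1 − p) | E |
|---|---|---|---|---|
| 6.3% | 1.530 | 0.1237 | 0.0590 | 0.26 |
| 8.6% | 1.366 | 0.1570 | 0.0786 | 0.31 |
| 16.5% | 0.974 | 0.2482 | 0.1378 | 0.45 |
| 50% | 0 | 0.3989 | 0.2500 | 0.64 |

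The median is the best case, so the loss is at least 36% under these assumptions. E does not depend on the number of climbers.

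**2. Like-for-like power.** Splitting multiplies a correlation by √E. With 55 climbers, two-sided 5% and Fisher's z:

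| Assumed true r | Continuous score | Median split | Split at 8.6% |
|---|---|---|---|
| 0.3 | 0.61 | 0.42 | 0.23 |
| 0.4 | 0.86 | 0.66 | 0.38 |

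Used continuously, 55 climbers detect r = tanh[(1.96 + 0.84)/√52] ≈ 0.37 with 80% power.

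**3. Size of the high group and detectable d** (80% power, two-sided 5%, noncentral t, one outcome):

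- 55 climbers, 8.6%: 55 × 0.086 = 4.7, so about 5 against 50; d ≈ 1.3.
- 200 climbers, 8.6%: 200 × 0.086 = 17.2, so about 17 against 183; d ≈ 0.7.
- 55 climbers, median split: 27 against 28; power 0.83 for d = 0.8.

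The sex-specific figures bracket the first line: 55 × 0.063 = 3.5 and 55 × 0.165 = 9.1. Each belongs to one sex, so a mixed sample with those prevalences would lie between them.

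**4. Effect of bone density in the same MANOVA.** If handling is complete-case, the share of climbers lost from the questionnaire outcomes is 1 − DEXA share. The shares below are assumptions.

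| DEXA share | Climbers lost | High-ED climbers left (55 climbers, 8.6%) |
|---|---|---|
| 30% | 70% | 55 × 0.30 × 0.086 = 1.4 |
| 50% | 50% | 55 × 0.50 × 0.086 = 2.4 |
| 70% | 30% | 55 × 0.70 × 0.086 = 3.3 |

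If every climber is scanned, as the text under Table 1 can be read, this loss is zero.

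**The case against.** A reader might infer that the high group is bound to be tiny and that the plan throws away most of the data. The document does not support either in that form.

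- High ED is never defined. A median split would give groups of 27 and 28 at 55 climbers, with reasonable power for a large difference.
- Fifty-five is a needed number for another comparison, not a cap. The whole eligible Swedish population is invited, and the Discussion expects a large sample.
- The cited prevalences come from other climber samples. The article does not say that they used EDE-Q with a cut at 2.5.
- The article does not spell out a single joint model or complete-case handling, and the DEXA share is unknown. Most climbers would be lost only if both applied and the share were below one half.
- The information figures assume normality, and the article gives no distribution of EDE-Q.
- The hypothesis is worded as a comparison of climbers with more and fewer symptoms, so a group contrast does address it. Multinomial regressions and a structural equation model are also planned.

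All of this limits the size of the problem and stands to that extent. It does not remove the problem. A larger sample restores power but not the share of information lost to the split. A median split still loses about 36% under normality, and it would match neither of the article's own cut-offs. The other planned models do not replace this comparison: the regressions address outcome trajectories, and the structural equation model comes later with injuries as its outcome. The plan does name bone density among the outcomes of the MANOVA, so one joint model is the natural reading.

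**Conclusion.** The point holds as a criticism of a stated method. Splitting a graded score loses information at any cut: under normality and linearity it keeps 64% at best and 26% to 45% over the cited prevalences. A very small high group (about 5 climbers, detectable d about 1.3) follows only if high ED means a score above 2.5, prevalence is near 8.6% and about 55 climbers enrol; with 200 climbers it is about 17 and 0.7. Loss of unscanned climbers from the questionnaire outcomes follows only if bone density shares a complete-case MANOVA with them, and it then equals one minus an unstated DEXA share. This concerns a secondary hypothesis and is inexpensive to correct, so it should be changed, but it does not threaten the study's primary comparison of climbers with controls.

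**What to change.** - Make the continuous EDE-Q global score the predictor in separate models for OSTRC-O, each DASS scale and RED-S symptoms, using all climbers.
- Analyse bone density in its own model in the DEXA subset. State the share of climbers to be scanned, and reconcile the Table 1 footnote with the text below it.
- Keep the cut-offs of 2.5 and 4 for descriptive prevalence. If a high/low grouping is kept anywhere, such as in the repeated-measures ANOVA, define it in advance.
- State how multiplicity is handled across the separate models, for example by Holm's procedure.

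No new data are needed, and the change is best made before the baseline analyses. The costs are that the high/low contrast becomes descriptive and that several tests replace one omnibus test. With one model each for injuries, RED-S symptoms and bone density and three for DASS there are 6 tests. The strictest Holm threshold is then 0.05/6 = 0.0083, and the detectable correlation with 55 climbers rises from about 0.37 to tanh[(2.64 + 0.84)/√52] ≈ 0.45 at that threshold. A significant MANOVA would also need follow-up tests to show which outcome differs, so this cost is not wholly new.

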#### Eating Disorders Examination Questionnaire

DE will be measured by the Eating Disorders Examination Questionnaire (EDE-Q 6.0),^33^ which is validated and includes 36 questions and records symptoms during the 28 days prior to filling in the questionnaire (eg, ‘Have you been deliberately trying to limit the amount of food you eat to influence your shape or weight (whether or not you have succeeded)?’. EDE-Q consists of four subscales (Restriction Scale, Eating Concern, Figure Concern and Weight Concern) as well as a score indicating global level of EDs symptoms. A cut-off score of >2.5 will be used as indicative of DE and >4.0 for EDs. EDE-Q has demonstrated adequate test–retest reliability (r=0.89) and internal consistency (α=0.85).^34^

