One limitation of our study is that we are using a non-random convenience sample that may not be representative to advanced rock-rock climbers in an international perspective. We have aimed to include the whole advanced level rock-climbing community in Sweden aged 15 years and older, which is the rationale for how the participants were recruited. According to the Swedish Climbing Association, there were 15 409 climbers affiliated to a climbing club in 2022. It is unknown, however, how many climbers are of an advanced or higher level, and thus eligible for participating in the study. Another potential limitation is the use of self-report questionnaires only which yield subjective data. Although the authors will encourage all participants to fill out all surveys using communication strategies at baseline and throughout the follow-up surveys, there is an undeniable risk of increased drop-out rates with each passing survey.

The climbing-concerned scientific community is at the beginning of forming a paradigm around this subject. The many facets of this study make CLIMB invaluable in gaining a holistic view on each participant as well as on group levels, which ultimately contributes to developing and implementing evidence-based interventions around the globe.

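### The one-way repeated-measures ANOVA has no group-by-time term, so it cannot test whether change differs between high-ED and low-ED climbers

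*Protocol article*

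**What the plan says.** The Data analysis plan of the protocol article first assigns MANOVA to the climbers-versus-controls comparison, and to a comparison of high-ED with low-ED climbers on bone density, injuries, mental health and RED-S symptoms. For the course over time it then says: "A one-way repeated measures ANOVA will be used to identify changes over the 2-year span in the two groups of rock climbers", the groups again being high and low ED. The next sentence sets the between-group step: "In cases where overall significant changes are detected, post hoc analysis will be applied to specify where the between-group differences exist". No group factor and no group-by-time term is named for this analysis. Neither the cut-off nor the visit that makes a climber high or low is tied to it, and its outcome variables are not listed.

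Three other places bear on it:

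- The same section plans multinomial logistic regression, which "will be used to determine the associations between each of the exposures and trajectories of outcomes".
- The Abstract promises sensitivity analyses for loss to follow-up.
- The Discussion concedes that "there is an undeniable risk of increased drop-out rates with each passing survey".

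**The concern.** The two sentences do not fit together. The first names a test whose only factor is time. The second expects that test, once significant, to lead to statements about differences between groups. If the plan is followed as written, there are two ways to proceed, and neither answers the question:

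- **One ANOVA on all climbers.** The F-test concerns the average change over both groups. It ignores how the groups differ in their change.
- **One ANOVA per group.** Each F-test concerns change within that group. One significant and one non-significant result is not evidence that the groups differ.

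At stake is the conclusion on whether climbers with more eating disturbance follow a different course over two years. A real difference could be missed because no overall change appears, and a general drift shared by both groups could be reported as a between-group finding.

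**Working it through.** **The plan's own figure.** The article gives no number for this analysis. Its only sample-size figure, about 55 per group, is for climbers versus controls and comes from "using a power of 80%, a significance level of 5% and an expected relative risk of 1.5 for the primary outcome". It cannot be reproduced from the stated inputs because no control-group risk is given, and it has no bearing on the choice of model. I use 55 climbers below for illustration only.

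**What each test looks at.** Let d1 and d2 be the mean changes in the high-ED and low-ED groups, of sizes n1 and n2.

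- One-way time test on all climbers: (n1·d1 + n2·d2)/(n1 + n2).
- Group-by-time test: d1 − d2.

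The first can be zero when the second is large. With 27 and 28 climbers, d1 = 0.5 SD and d2 = −0.5 × 27/28 = −0.48 SD, the pooled change is 0 and the difference is 0.98 SD. The reverse also holds: with d1 = d2 = 0.4 SD, the pooled change is 0.4 and the difference is 0.

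**Simulation.** Assumed inputs: 4,000 runs, visits at 0, 0.5, 1 and 2 years, change linear in time, SD 1, within-person correlation 0.6, no missing data, 5% level. Changes are over two years, in SD, high group first.

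| Split | Changes | Pooled change | Difference | One-way time test rejects | Group-by-time test rejects | Separate tests disagree |
|---|---|---|---|---|---|---|
| 27/28 | 0, 0 | 0 | 0 | 5% | 5% | 10% |
| 27/28 | 0.4, 0.4 | 0.4 | 0 | 83% | 5% | 50% |
| 27/28 | 0.5, −0.48 | 0 | 0.98 | 4% | 95% | 42% |
| 27/28 | 0.5, 0 | 0.25 | 0.5 | 38% | 43% | 68% |
| 11/44 | 0.4, 0.4 | 0.4 | 0 | 83% | 5% | 64% |
| 11/44 | 0.5, −0.125 | 0 | 0.625 | 5% | 39% | 34% |
| 11/44 | 0.5, 0 | 0.10 | 0.5 | 9% | 27% | 32% |

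The last column is the share of runs in which a one-way test in each group gives one significant and one non-significant result. With equal true change it does so in 50% to 64% of runs.

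**Complete rows.** The classical procedure by default keeps only climbers with every survey. The listed schedule has three follow-ups within two years (6 months, 1 year, 2 years). The article gives no drop-out rate, so I assume 10% or 20% loss per wave:

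- 55 × 0.90³ = 55 × 0.729 = 40 completers.
- 55 × 0.80³ = 55 × 0.512 = 28 completers.

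**Regression to the mean, only if EDE-Q is the outcome and the groups are split on baseline EDE-Q.** If the high group is the top 8.6% to 16.5% of a normal distribution (disordered-eating proportions that the article cites for climbers), its mean lies 1.83 to 1.50 SD above the overall mean. With no true change, the expected fall is (1 − r) times that:

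- at the article's test–retest r = 0.89: 0.11 × 1.50 to 0.11 × 1.83 = 0.17 to 0.20 SD;
- at an assumed two-year correlation of 0.7: 0.30 × 1.50 to 0.30 × 1.83 = 0.45 to 0.55 SD.

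**The case against.** The strongest reply is that the ANOVA sentence promises only to identify changes in the two groups. A one-way test run in each group can do that, and within-group change bears on the expectation in the Introduction that patterns are stable over time. The trajectory regression is a second longitudinal analysis, and disordered eating is among its listed exposures. A reader might therefore be tempted to say that the longitudinal question goes unanswered altogether. The article does not support that: what is missing is a test of the difference in change. The reply still fails on the next sentence, which draws between-group differences from the ANOVA. The trajectory regression does not supply the group-by-time test that this step needs.

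A reader might also infer that every climber with a missed survey will be dropped. No section says so. It is the default of the classical method, imputation is not ruled out, sensitivity analyses for loss to follow-up are promised, and details may sit in an analysis plan not shown. Nor does the article say that drop-out will be heavier among climbers with symptoms. Completer counts after five follow-ups do not apply, since this analysis covers two years, and 55 is a calculated requirement, not the expected enrolment.

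Finally, a reader might call any fall in the high-ED group an artefact. That needs EDE-Q as the outcome and a split on baseline EDE-Q, and the article states neither for this analysis.

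**Conclusion.** The point holds in this form: the named ANOVA cannot test whether change differs between high-ED and low-ED climbers, and gating that comparison on an overall change can fail in both directions. This follows from the structure of the test and needs no assumption. The sizes (4% versus 95% rejection when changes cancel, 83% versus 5% when change is equal) rest on the assumed correlation, split and pattern of change, and illustrate the failure without predicting it. The completer counts of 40 or 28 rest on assumed drop-out rates and on the method's default handling. Regression to the mean remains conditional.

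This should be fixed, but it is not a threat to the whole study. The main hypothesis compares climbers with controls, who are measured at baseline only, and this ANOVA plays no part in it.

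**What to change.** Replace the one-way ANOVA and its gated post hoc step, for each outcome measured repeatedly (bone density is taken at baseline only), with a model containing group (high versus low ED at baseline, with the cut-off stated), time as a categorical factor, and group-by-time. Test the interaction as the between-group difference in change, whether or not the overall time effect is significant, and report the estimated difference with its 95% CI.

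A mixed ANOVA with a group factor would repair the inconsistency. A linear mixed model is preferable because it uses all available observations when surveys are missed. Check its fit for bounded scores such as OSTRC-O (0 to 100). If EDE-Q is itself an outcome, model it over time in all climbers, not as change within groups cut on its baseline value.

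Two limits remain. A non-significant interaction does not establish stability, so the interval should be read for that. Power may also be modest: in the simulation, a 0.5 SD change in the high group alone was detected in 43% of runs (27/28 split) or 27% (11/44).

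The cost is revised wording and slightly more modelling, with no new data. The Study status section places baseline analyses first, so the change can be made before the follow-up data are analysed.

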Our main hypothesis is that elite and advanced rock climbers will present more DE symptoms compared with controls, with elite rock climbers showing more symptoms than advanced rock climbers. A secondary hypothesis is that rock climbers who report more eating disturbances will present with higher levels of health problems including decreased bone density, CE, depression, body dissatisfaction, menstrual disturbances and more overuse injuries as compared with rock climbers with less symptoms of eating disturbances, as these secondary variables are correlates of EDs.^32^ We expect these patterns to be stable over time. The authors will also examine the gender differences in these categories and expect, for example, to find higher percentages of DE among women than men, following the pattern of the presented literature. At the time of writing, there exists sparse research on the connection between rock climbing, DE and energy deficiency. The presented hypotheses are therefore largely grounded on findings in other sports with similar bodily and/or weight requirements, such as ballet, figure skating and gymnastics. Due to the rapidly increasing popularity of recreational and competitive climbing, longitudinal cohort studies are, therefore, urgently needed to understand the aetiology of health problems related to EDs in rock climbers in particular. Studies that identify risk and prognostic factors are required to develop health promotion and disease prevention strategies, which ultimately can reduce the burden of disease in rock climbers worldwide.

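### Change is tested within high-ED and low-ED climbers; if these groups are set on one survey's EDE-Q and followed on the EDE-Q, regression to the mean will pass for change

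*Protocol article*

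**What the plan says.** The Data analysis plan first compares climbers with high and low ED on bone density, injuries, mental health and RED-S symptoms. It then applies a one-way repeated measures ANOVA to "identify changes over the 2-year span in the two groups of rock climbers with high ED versus low ED". An overall significant change leads to post hoc tests.

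The Outcome section says "The outcome ED will be measured with the EDE-Q", so the groups rest on the EDE-Q. That section also names EDE-Q symptoms as a primary outcome, and Table 1 repeats the EDE-Q at every follow-up. The instrument section says that it "records symptoms during the 28 days prior to filling in the questionnaire" and gives a test-retest reliability of 0.89 without the retest interval. It also gives two thresholds: "A cut-off score of >2.5 will be used as indicative of DE and >4.0 for EDs". Neither is tied to the high/low split.

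The article does not state the survey at which a climber is classified, the dividing score, whether membership is fixed or updated, or the variable that the ANOVA follows. Controls are not followed up (Study design and participants). The Introduction says of the hypothesised patterns: "We expect these patterns to be stable over time".

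**The concern.** A group chosen because it scored high on one occasion will, on average, score lower on the next occasion even if every member's underlying level is constant, because part of the high score was error or a passing fluctuation. The low group moves up in the same way. If the ANOVA follows the score that formed the groups, this movement enters the time effect and is tested as change. A group-by-time model would carry the same bias, so the problem lies in the selection and not in the one-way form of the test.

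At stake is the reading of the longitudinal result: an apparent easing of symptoms in symptomatic climbers, and a narrowing gap between the groups, with no one having changed. No safeguard is described, and without followed controls there is no concurrent series that might show it.

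**Working it through.** The article gives no figure for this analysis, so there is none to reproduce. The check asks how large the artefact is when no true change occurs.

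**Inputs**
- Test-retest correlation r = 0.89 (EDE-Q instrument section; interval not given).
- Share above the cut-off p = 0.086. This is the disordered-eating rate in the earlier survey of 604 climbers cited in the Introduction. It is not stated to be a rate of EDE-Q above 2.5, so its use here is an assumption.
- Bivariate normal scores with the same mean and SD at both surveys (assumption; it ignores the floor and skew of the EDE-Q).
- Groups fixed on one survey's EDE-Q and followed on the EDE-Q (the condition under examination).

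**Mean shift.** For p = 0.086 the cut-off is z = 1.366, where the normal density φ(z) is about 0.157.
- Fall in the high group = (1−r)·φ(z)/p = 0.11 × 0.157/0.086 = 0.20 SD.
- Rise in the low group = (1−r)·φ(z)/(1−p) = 0.11 × 0.157/0.914 = 0.019 SD.
- The gap starts at 0.157/0.086 + 0.157/0.914 = 1.83 + 0.17 = 2.00 SD and shrinks by 0.20 + 0.02 = 0.22 SD, which is 11%, or 1−r.

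**Crossing the cut-off.** The bivariate normal gives P(above at the next survey | above at the first) = 0.661, so about 34% of high scorers are then below it.

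**Sensitivity**
- p = 0.165 (the female rate cited in the Discussion) with r = 0.89: fall 0.17 SD, 28% below the cut-off.
- p = 0.086 with an assumed long-interval r of 0.7 or 0.6: fall 0.55 or 0.73 SD, 55% or 63% below.
- In EDE-Q points with cut-off 2.5, r = 0.89 and assumed mean/SD from 0.8/0.9 to 1.5/1.3: fall 0.19 to 0.23 points, 25% to 42% below.

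**Effect on the test.** One-way repeated measures ANOVAs were simulated 3,000 times per setting with four visits (baseline, 6 months, 1 and 2 years), perfectly stable true scores, groups fixed at baseline, and assumed mean and SD of 1.2. This puts 13.9% above 2.5. The 55 climbers are the per-group figure from the Sample size section, used only for scale. Rejection rates at a nominal 5%:

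| Climbers | r | High group | Low group | All climbers undivided |
|---|---|---|---|---|
| 55 | 0.89 | 14.5% | 6.2% | 4.7% |
| 55 | 0.7 | 36.5% | 8.2% | 4.3% |
| 200 | 0.89 | 51.0% | 11.4% | 5.3% |
| 200 | 0.7 | 94.1% | 22.0% | 4.9% |

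A median split does not avoid the problem: with 55 climbers and r = 0.89 it gives about 14% in each group. Analysed undivided, climbers stay near 5%.

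**The case against.** The strongest reply is that the sentence names no followed variable. The one before it concerns bone density, injuries, mental health and RED-S, and disordered eating is listed among the main exposures. The analysis may therefore be an exposure-defined cohort followed on other outcomes. The classification survey, the cut-off and the membership rule may also stand in a fuller plan that is not shown.

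Much of this stands, and it makes the point conditional. On the exposure reading, regression to the mean reaches mental health, RED-S symptoms and injuries only through transient fluctuation shared with the EDE-Q, and is weaker. Bone density, measured only at baseline, is untouched. What remains is that the stated analysis tests change in groups resting on a repeated primary outcome, and nothing in the text excludes following that outcome.

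A reader might infer more than the text supports:
- **That climbers are split at 2.5 with fixed membership.** The article says neither.
- **That the plan would report recovery.** With 55 climbers and r = 0.89, about 85% of such analyses would show no significant change in the high group.
- **That the stability hypothesis would be wrongly rejected.** The patterns in the Introduction are group differences and associations, not a constant EDE-Q mean in each group. The artefact bears on them by narrowing the high-low gap.
- **That crossing the cut-off is a second fault.** With fixed groups it is the same artefact as the mean shift.
- **That the results at r = 0.6 to 0.7 are all artefact.** Those correlations are assumed, and a drop from 0.89 over one or two years may partly be real symptom change.

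**Conclusion.** The point holds conditionally. If high and low ED are set on one survey's EDE-Q and the EDE-Q is then followed, the plan as worded will produce a spurious fall in the high group and a gap narrowed by about 1−r. At the article's own reliability the bias is modest: about 0.20 SD in the high group and 0.02 SD in the low group. It is still enough to roughly triple the false-positive rate in the high group with 55 climbers (about 15% against 5%), and the inflation grows with more climbers or a lower long-interval correlation. The figures rest on normality, an assumed 8.6% above the cut-off for the SD results, and an assumed mean and SD of 1.2 for the error rates. They are illustrative. This is a cheap improvement to the analysis, not a flaw that invalidates the study.

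**What to change.** Do not test EDE-Q change within groups selected on the EDE-Q. Estimate EDE-Q change over time in all climbers as one cohort, with a repeated-measures or mixed model. Relate the other repeated outcomes (mental health, RED-S symptoms, injuries) to the EDE-Q as a continuous score. Report movement across 2.5 only as a descriptive transition table: stayed low, low to high, high to low, stayed high. Do not benchmark that table against r=0.89, because the retest interval behind that value is not given. If a high-versus-low display is kept, state the survey used for classification, the cut-off and the variable followed.

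The cost is a change of analysis wording. The EDE-Q is already collected at every climber survey. The downside is that the high-versus-low comparison over time becomes descriptive.
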